**Fig. 4 Fig4:**
[figure not shown]
Patients' schedule of trial enrollment, interventions, and assessment. DXA, Dual X-ray Energy Absorptiometry; BIA, Bioelectrical Impedance Analysis; SarQoL-K, Korean version of the Sarcopenia Quality of Life; SF-36, 36-Item Short Form Survey; PHQ-9, Patients Health Questionnaire-9; BDI, Beck Depression Inventory, CTX: C-telopeptide (type 1 collagen). ^*^Blood lab analysis: Albumin, Pre-albumin, Aspartate Aminotransferase; AST, Alanine Aminotransferase; ALT, Alkaline Phosphatase; ALP calcium, Creatinine, Blood Urea Nitrogen; BUN, 25(OH) Vitamin D, Parathyroid hormone. ^†^Nutritional support: 2 packs of protein complex powder (Selex core-protein; protein: 20 g, vitamin D: 800 IU, calcium: 300 mg, fat: 1.1 g, carbohydrate: 2.5 g; Maeil Dairies Co., Ltd., Seoul, South Korea) will be provided

### Primary outcome measurement

The primary outcomes of this trial will be changes in the SMI and BMD of the lumbar spine and total hip using DXA (Hologic, Marlborough, Massachusetts, USA) analysis from the baseline to end of intervention (24 weeks). Changes in body composition will be repeatedly measured at T0 (0 weeks), T2 (12 weeks), and T4 (24 weeks) to evaluate the effects of resistance training and nutritional support, as well as whether the effect gain by the intervention is maintained after training (Fig. 4).

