### Sample size calculation

The sample size was determined using SMI changes. A previous study demonstrated that the 28-week intervention with HI-RT and protein supplementation changed the SMI, with values of -0.03 ± 0.21 in the control group and 0.30 ± 0.22 in the intervention group [14]. A two-tailed, T-test-based sample test was performed according to the previous trial; the calculated sample size of 13 participants per group corresponds with a 95% power (1-β), type-I alpha error =0.05, and effect size of d=1.53. We decided to include at least 17 people each group, assuming a 25% dropout rate.

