### Statistical analysis

All analyses will be carried out using IBM SPSS Statistics (version 23.0; IBM, Armonk, New York, USA), with a significance level of 5% and a 95% CI. Descriptive statistics will be applied to present the subject demographics. Intention-to-treat analysis will be performed to analyze the results, and the independent T-test will be used to compare the baseline values between groups. For the analysis of primary outcomes, independent t-test or Mann-Whitney U test for comparisons between changes from the baseline to the end of the intervention will be applied according to the distribution of data by Shapiro-Wilk test. The data will be described using means, standard deviations, and 95% confidence intervals (CIs). The method for handling missing data will be chosen after the study is finished based on the distribution of the data. A mixed-effects model or generalized estimating equations will be employed using one between-subject factor (group: intervention and control) and one within-subject factor to compare the secondary outcomes and find differences in outcomes between groups with time.

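### No pre-specified primary analysis uses the week-12 measurement, so at the planned 25% dropout some precision, and protection against response-related dropout, is left unplanned

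*Protocol article*

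**What the plan says.** All references are to the protocol article.

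- **Primary outcome measurement.** SMI and bone mineral density (BMD) of the lumbar spine and total hip are assessed by DXA "analysis from the baseline to end of intervention (24 weeks"). The next sentence has changes in body composition "repeatedly measured at T0 (0 weeks), T2 (12 weeks), and T4 (24 weeks) to evaluate the effects of resistance training".
- **Statistical analysis, primary outcomes.** "independent t-test or Mann-Whitney U test for comparisons between changes from the baseline to the end of the intervention will be applied", the choice between the two depending on a Shapiro-Wilk test.
- **Statistical analysis, repeated measures.** "A mixed-effects model or generalized estimating equations will be employed using one between-subject factor (group: intervention and control") plus one within-subject factor, "to compare the secondary outcomes and find differences in outcomes between groups with time".
- **Statistical analysis, missing data.** Intention-to-treat is promised. The method for missing values is to be selected once the study has ended.
- **Sample size calculation.** 13 per group, raised to at least 17, "assuming a 25% dropout rate".

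**The concern.** The week-12 measurement appears in the primary-outcome section with the stated aim of evaluating the effect, yet the primary analysis does not use it. This is more than detail left to a fuller document: the article names the primary test and assigns the repeated-measures model to the secondary outcomes.

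A two-sample test on week-24 change cannot include a woman without a week-24 value unless something is imputed, and no imputation is planned. Non-completion is also listed among the exit criteria, so losing such women is a real prospect.

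Two things are at stake:

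- **Precision.** Week-12 change predicts a missing week-24 change to the extent that the two are correlated.
- **Bias.** Participants in the exercise arm are not blinded, and training intensity steps up again in phase 3, after the week-12 visit. If women who had gained little by week 12 are the ones who leave, those who remain make the exercise arm look better than it is.

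**Working it through.** **The plan's own figure.** Inputs from Sample size calculation: SMI change −0.03 (SD 0.21) in controls and 0.30 (SD 0.22) with exercise.

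- Difference = 0.33. Pooled SD = √[(0.21² + 0.22²)/2] = 0.215. d = 0.33/0.215 = 1.53, as stated.
- Two-sided t-test, α = 0.05, noncentral t: power is 94.7% at 12 per group and 96.2% at 13. So 13 is reproduced.
- With 17 per group and 25% lost, 17 × 0.75 = 12.75 completers per group are expected.

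**Assumption.** The correlation r between week-12 and week-24 change is not given. A range of 0.3 to 0.9 is used.

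**Precision, random dropout.** Let q = 0.25 be missing at week 24, all with a week-12 value. The variance of the week-24 mean under a likelihood analysis using week 12, relative to completers only, is

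[(1 − r²)/(1 − q) + r²] × (1 − q) = 1 − r²q.

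If half the leavers go before week 12, week 12 is observed in 87.5% and the ratio is 1 − r² + r² × 0.75/0.875.

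| r | Ratio, all leavers scanned at week 12 | SE reduction | Effective n per arm (12.75/ratio) | Ratio, half scanned | SE reduction |
|---|---|---|---|---|---|
| 0.3 | 0.978 | 1.1% | 13.0 | 0.987 | 0.6% |
| 0.5 | 0.938 | 3.2% | 13.6 | 0.964 | 1.8% |
| 0.7 | 0.878 | 6.3% | 14.5 | 0.930 | 3.6% |
| 0.9 | 0.798 | 10.7% | 16.0 | 0.884 | 6.0% |

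These are large-sample values. A simulation with 17 per arm (5,000 runs per setting, separate regression of week-24 on week-12 change in each arm) gave these SEs, completers only versus using week 12:

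- r = 0.3: 0.0866 versus 0.0872, so no gain.
- r = 0.5: 0.0877 versus 0.0862.
- r = 0.7: 0.0858 versus 0.0806.
- r = 0.9: 0.0863 versus 0.0774.

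**Complete data.** The two estimators coincide. The simulated SE is 0.073 to 0.074 for both, matching 0.215 × √(2/17) = 0.0737.

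**Bias, dropout depending on week-12 gain.** Completer bias = r × SD × (mean standardised week-12 deviation among those retained in the exercise arm).

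- *Graded pattern.* The exercise-arm dropout probability is 1/(1 + exp(1.35 + 1.5z)), where z is the standardised week-12 change. About 27.6% are lost; control loss is random at 25%. The retained mean of z is 0.303, so the bias is 0.303 × 0.215 × r = 0.020, 0.033, 0.046 and 0.059 kg/m² for r = 0.3, 0.5, 0.7 and 0.9. The simulation gave 0.020, 0.032, 0.044 and 0.059, or 6% to 18% of 0.33.
- *Extreme pattern.* The four lowest week-12 gainers of 17 leave. The retained mean of z is 0.38, so the bias is 0.38 × 0.215 × r = 0.041 at r = 0.5 and 0.069 at r = 0.85. A separate simulation gave 0.041 to 0.070, or 12% to 21% of 0.33.
- *With week 12 used.* Bias is about zero if every leaver has the week-12 scan. If only two of the four leavers have it, 0.009 to 0.023 kg/m² (3% to 7%) remains.
- *Type I error.* With no true effect and the graded pattern, the completers' t-test rejects in 7.2%, 8.1% and 10.8% of runs at r = 0.5, 0.7 and 0.9, against a nominal 5%.

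Under the graded pattern the week-12 estimator is slightly more variable than the completer estimator at low r (0.0905 against 0.0862 at r = 0.3). The main benefit is therefore protection from bias, with precision second.

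**The case against.** The strongest case on the other side has five parts.

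1. **The stated analysis is coherent.** The outcome is defined as a two-time-point change, the sample size rests on a t-test, and the t-test is applied to that change. This stands: the planned test is valid for its outcome, and even 13 completers per group give 96.2% power on the planning assumptions.
2. **Week 12 is not ruled out.** A reader might infer that the week-12 value is discarded and that a woman without a week-24 scan contributes nothing. The document does not say so. It promises intention-to-treat and leaves the missing-data method open. Multiple imputation using week 12, followed by the planned t-test, would also use it, so a repeated-measures model is not the only route. This stands. What remains is that a method chosen after the data are in is not pre-specified protection.
3. **The week-12 measure might be BIA.** The secondary outcomes include body composition by BIA, which the mixed model or GEE would already cover. However, the three-visit sentence directly follows the naming of DXA under the primary heading, and BIA has its own section. DXA is the natural reading for SMI, though not a certain one. A reader might extend the point to BMD, but no week-12 BMD scan is stated, and Fig. 4, which could settle it, is not shown in the text reviewed.
4. **The secondary outcomes are not clearly better served.** The plan leaves open a mixed model or GEE. Ordinary unweighted GEE does not in general protect when dropout depends on earlier response. This stands, and the remedy must be specific about the model.
5. **The bias figures are conditional.** They need dropout tied to week-12 response in one arm, and a correlation the document does not supply. This stands too; the upper end requires the four weakest responders to be exactly the four who leave.

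**Conclusion.** The concern holds in a limited form: no pre-specified primary analysis uses the week-12 measurement. The cost is conditional.

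- **Complete week-24 data:** none.
- **25% random dropout:** the forgone reduction in the SE of the SMI difference is roughly 1% to 11% for r from 0.3 to 0.9 if all leavers have the week-12 scan. It is about half that if only half do, and negligible at the low end with 17 per arm.
- **Poor week-12 responders leaving the exercise arm:** a completers' comparison is biased upward by roughly 0.02 to 0.07 kg/m². Using week 12 removes or reduces this only for women who had that scan.

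The correlation and the dropout pattern are assumptions. No size can be given for BMD. The documents do not support the reading that precision and protection are lost outright, or that the planned test is wrong. This is an inexpensive improvement worth making before analysis.

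**What to change.** In Statistical analysis, state that SMI, and BMD if Fig. 4 shows it is scanned at week 12, will be analysed with a likelihood-based linear mixed model (not GEE) using all scheduled DXA scans. Specify categorical time, group and group-by-time with arm means free at each visit, unstructured covariance, REML and small-sample degrees of freedom. Name the week-24 between-group difference in change as the primary estimate and treat week 12 as supportive. Keep the t-test or Mann-Whitney comparison of change as a sensitivity analysis. In Primary outcome measurement, say explicitly which DXA quantities are taken at week 12.

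The cost is a few sentences. No added visits, scans, participants or software are needed, and a mixed model is already one of the two options planned for the secondary outcomes. The price is a missing-at-random assumption and a few covariance parameters (six for three visits) in a trial of 34. With complete data the point estimate equals the simple difference in mean change.

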### Secondary outcome measurement

#### Body composition and phase angle measurement by BIA

Body compositions, such as a lean body mass, body fat (%), and appendicular skeletal muscle mass, will be analyzed using multi-frequency BIA (S10; Inbody, Seoul, South Korea). The detailed protocol for BIA measurement follows the guidelines provided in the manufacturer's manual and is also informed by a previous study [24]. Before the BIA measurement, patients will be instructed not to eat, drink, or engage in resistance exercise for at least 2 hours. The BIA measurement will be conducted with patients in a supine position. The whole-body phase angle of the participants will be assessed by BIA four times every 6 weeks from the beginning to end of the intervention (Fig. 4) [25].

#### Quality of life and psychological assessment

The quality of life and depression status of participants will be measured using the Sarcopenia Quality of Life (SarQoL-K), 36-Item Short Form Survey, Patients Health Questionnaire-9 (PHQ-9), and Beck Depression Inventory (BDI).

The SarQoL-K questionnaire comprises twenty-two scaled questions and assesses the quality of life in community-dwelling elderly individuals aged 65 years and older who have sarcopenia. The questionnaire has been translated and validated in Korean [26] with scores ranging from 0 to 100.

The 36-Item Short Form Survey contains eight scaled scores and is a patient-reported survey regarding overall health, with scores ranging from 0–100; a higher score corresponds with a favorable health status [27].

The PHQ-9 and BDI are patient-reported questionnaires evaluating the depression status of participants. The PHQ-9 comprises nine items on a 4-point scale ranging from 0–3. A cutoff of 10 points is considered to indicate depression. The Korean PHQ-9 was validated in the older people [28], and will be used to assess the depression status of participants.

The BDI is one of the most widely used self-reported questionnaires for evaluating the severity of depression [29]. Twenty-one questions with multiple choices will be assessed and scored, with values of 0–3 for each question; the total score is therefore 0–63. Higher scores indicate more depressive symptoms in participants. The BDI has also been translated into a Korean version, and was proven to be reliable and valid for screening patients in older people [29].

#### Physical performance assessment

The physical performance of participants will be measured by handgrip strength (known to be a significant indicator of overall body strength, functional status, and even nutritional status [30–32]), the Berg Balance Test (BBT), and SPPB. Handgrip strength will be measured in the dominant hand using a handheld dynamometer (Jamar; Hoggan Scientific, Salt Lake City, Utah USA). All participants will be asked to sit in chair, adduct their shoulder, and flex their elbow 90°. They will then be asked to squeeze their hand to achieve the maximum effort isometric contraction; this will be repeated in triplicate, and the maximum reading of the gauze will be recorded, as previously recommended in Asian Working Group for Sarcopenia guidelines [11].

The BBT evaluates the functional balance of participants [33]. It evaluates both dynamic and static balance via 14 tasks. Each task is graded on a 5-point scale ranging from 0–4; the maximum score is 56 points, with a higher score indicating better balance and a lower chance of falls in the older people [34].

The SPPB is a widely used scale for evaluating the strength of the lower extremities, 4-m walking speed at usual pace, and static standing balance [35]. The SPPB is associated with falls reported in the older people, as well as mobility and disability [36]. The SPPB will be measured according to the standard previously reported [35]. Three tasks will be given to patients to complete in order to measure their standing balance, 4-m walking speed, and time to complete the Five Times Sit-to-Stand test. The SPPB's overall score scales from 0 to 12, with a higher score suggesting better participant performance.

#### Muscle quality index

The MQI is calculated from the common sit-to-stand test and reflects both the muscle power and informative functional index, incorporating the velocity of muscle shortening and anthropometric measures [37]. The MQI is calculated as follows [38]: MQI = ((leg length - 0.4) × body mass × gravity × 10) / time of sit-to-stand.

Using the taping method, the leg length is determined in this equation as the distance from the lateral malleolus to the greater trochanter of the femur. Body mass is measured in kilograms, the force of gravity is represented as 9.8 m/s^2^, and the time to complete the sit-to-stand test is the recorded time during the 10th repetition of sitting to standing in a standard chair from the sitting position. The MQI is validated and reliable [38], and reflects functional changes due to resistance exercise in the older people [37].

#### Bone turnover marker

We will measure bone turnover markers at three time points (T0, 0 weeks; T2, 12 weeks; T4, 24 weeks) during and immediately after the intervention to evaluate the effect of the intervention on bone metabolism. CTX is a known bone resorption marker, and higher levels are adversely associated with bone loss [39]. Fasting blood samples will be collected from the antecubital veins of participants, and CTX will be assayed via the Roche Cobas E801 electrochemiluminescence immunoassay (Roche Diagnostics, Basel, Switzerland) using the Elecsys beta-CrossLaps serum assay [40].

### Sample size calculation

The sample size was determined using SMI changes. A previous study demonstrated that the 28-week intervention with HI-RT and protein supplementation changed the SMI, with values of -0.03 ± 0.21 in the control group and 0.30 ± 0.22 in the intervention group [14]. A two-tailed, T-test-based sample test was performed according to the previous trial; the calculated sample size of 13 participants per group corresponds with a 95% power (1-β), type-I alpha error =0.05, and effect size of d=1.53. We decided to include at least 17 people each group, assuming a 25% dropout rate.

### Data management

Our research team will collect and process all data from participants, which will be stored on a platform accessible to the research team alone. All obtained information will be retained for 5 years. The backup database will be regularly updated. The anonymized dataset will be made available upon request to the corresponding author.

### Statistical analysis

All analyses will be carried out using IBM SPSS Statistics (version 23.0; IBM, Armonk, New York, USA), with a significance level of 5% and a 95% CI. Descriptive statistics will be applied to present the subject demographics. Intention-to-treat analysis will be performed to analyze the results, and the independent T-test will be used to compare the baseline values between groups. For the analysis of primary outcomes, independent t-test or Mann-Whitney U test for comparisons between changes from the baseline to the end of the intervention will be applied according to the distribution of data by Shapiro-Wilk test. The data will be described using means, standard deviations, and 95% confidence intervals (CIs). The method for handling missing data will be chosen after the study is finished based on the distribution of the data. A mixed-effects model or generalized estimating equations will be employed using one between-subject factor (group: intervention and control) and one within-subject factor to compare the secondary outcomes and find differences in outcomes between groups with time.

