**Methods:**

This research proposal presents the protocol for a prospective, single-center, single-blinded, two-armed randomized controlled trial. Thirty-four participants with osteosarcopenia will be recruited and randomly divided into intervention and control groups; both groups will receive nutritional supplements (protein, 40 g; vitamin D, 1600 IU; calcium, 600 mg) daily. The intervention group will undergo 24 weeks of resistance exercise of increasing intensity, achieved through a three-phase step-up process. The primary outcomes will be the changes in skeletal muscle index and bone marrow density of the lumbar spine and femoral neck between the baseline and end of intervention (24 weeks). The secondary outcomes will be the body composition, whole body phase angle, physical function assessment, quality of life, psychological assessment, and bone turnover markers of participants, surveyed at multiple time points.

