Sedentary lifestyles and poor nutritional status—including protein, vitamin D, and calcium—are known to be key risk factors for OS [13]. Controlling these risk factors may be key to maintaining the quality of bone and muscle tissue in geriatric patients, and perhaps even reverse the pathologic conditions causing these catastrophic results. The FrOST Study (Franconian Osteopenia and Sarcopenia Trial) aimed to evaluate the effect of high-intensity resistance exercise (HI-RT) and protein supplementation on the quantity of bone and muscle in male patients with OS [14]. The trial reported the effects of HI-RT supplemented with protein (1.5 g/kg/day in the HI-RT group and 1.2 g/kg/day in the control group) and vitamin D (800 IU/day), demonstrating improvements in the Z-score for SP (standardized mean difference [SMD]: 1.40), BMD at the lumbar spine (SMD: 0.72) and total hip (SMD: 0.72), and functional parameters (hand grip strength and gait speed) after 18 months of the intervention [15]. Moreover, they demonstrated the safety of the interventions; most participants completed the intervention program, excluding one male who reported a short period of worsening arthritic pain. Due to the COVID-19 lockdown period, the same authors also evaluated the detraining effects of the same study population for approximately 6 months, finding that the intervention group lost approximately one-third of benefits gained from the intervention, and exhibited higher detraining effects than the control group [16]. These trials suggest that a combination of exercise and nutritional support could prevent a further decline in bone and muscle health, and even reverse the pathological conditions; however, continuous management may be the key to managing these patients.

Our study aimed to determine the effects of multidisciplinary interventions—including resistance exercise and nutritional support (protein, vitamin D, and calcium)—to halt or reverse the decremental aging process affecting the quantity and quality of bone and muscle in postmenopausal females with OS.

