### Outcome measurement and participants’ timeline

The primary outcomes of this study are changes in the skeletal muscle index (SMI) and BMD of the lumbar spine and total hip between the baseline and end of the intervention. The SMI is an indicator of skeletal muscle mass, which is calculated as the appendicular skeletal muscle mass divided by height squared (kg/m^2^). The secondary outcomes are quality of life measurement, functional assessment, bone turnover marker (C-telopeptide [type 1 collagen], CTX), BIA assessment (including body composition and whole-body phase angle), and muscle quality index (MQI). Participants will be screened for adverse events from study inclusion, to the end of the intervention. The schedule of the trial is illustrated in Fig. 4. After obtaining informed consent, basal measurements including demographic details (sex, age, height, weight, alcohol consumption, smoking history, and other medical history) will be surveyed by the research delegate. Weight (kg) divided by the height squared (cm^2^) will be used to compute the body mass index (BMI). Blood samples in fasting status will be collected from the antecubital veins of participants, and analyzed within 24 h of sampling. Albumin, pre-albumin, calcium, parathyroid hormone, serum vitamin D, creatinine levels will be evaluated at T0 (0 weeks).

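### Three primary outcomes share one unadjusted 5% level with no success rule, and only SMI was sized: family-wise error is up to 14.3% if any one suffices, and BMD power is 42% to 53% at the only effect size quoted

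*Protocol article*

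**What the plan says.** - **Primary outcomes.** Outcome measurement and participants' timeline lists "changes in the skeletal muscle index (SMI) and BMD of the lumbar spine and total hip" as primary, and Primary outcome measurement repeats this for 24 weeks. The abstract's Methods paragraph gives a different hip site: "changes in skeletal muscle index and bone marrow density of the lumbar spine and femoral neck".
- **Test and level.** Statistical analysis runs all analyses "with a significance level of 5% and a 95% CI". For the primary outcomes, in the plural, it specifies the "independent t-test or Mann-Whitney U test for comparisons between changes from the baseline to the end of the intervention". It does not order the three outcomes, adjust for their number, or say whether one, any or all must be significant.
- **Sizing.** Sample size calculation states: "The sample size was determined using SMI changes". It gives 13 per group for 95% power at d = 1.53, raised to at least 17 per group for 25% dropout. No power is stated for BMD.
- **BMD effect.** The Background reports one BMD effect size, a standardised mean difference of 0.72 at both lumbar spine and total hip, from an earlier trial in men after 18 months of intervention.
- **Caveat.** The Discussion notes in general terms that the small sample could lower statistical power. It does not say which outcomes are affected.

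**The concern.** Three outcomes have equal primary status, each is tested at 5%, and nothing fixes what a positive trial is. Two readings are open, and each has a cost. If one significant result is enough, the chance of a false positive claim is above 5%. If all three must be significant, the sample is far too small unless the BMD effect is much larger than the one quoted. With no rule written down, the choice between these readings could be made after the results are known.

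The sample size does not settle this. It supports a confirmatory conclusion on SMI, but the two BMD outcomes carry the same label without a calculation behind them. The trial's aim covers bone as well as muscle, so this determines what it may claim about bone.

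**Working it through.** **1. Reproduce the plan's own figure (SMI).** Inputs from Sample size calculation: change −0.03 (SD 0.21) in control and 0.30 (SD 0.22) with intervention, two-sided 5%, 1:1.

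- Pooled SD = √((0.21² + 0.22²)/2) = 0.215; d = 0.33/0.215 = 1.53.
- Power of a two-sample t-test: df = 2n − 2, noncentrality = d·√(n/2), rejection when |T| exceeds the 97.5% point of t.
- n = 12 per arm gives 94.7%; n = 13 gives 96.2%. So 13 is the smallest n reaching 95%, as stated.
- With 17 enrolled and 25% lost, 17 × 0.75 = 12.75, so about 13 per arm complete. If all 17 are analysed, SMI power is 99.1%.

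**2. Family-wise error if any one significant primary outcome counts.**

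- Independent tests: 1 − 0.95³ = 0.1426, or 14.3%.
- The documents give no correlations between the outcomes, so a range is assumed. Simulation of three normal test statistics with a common correlation gives:

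| Common correlation (assumed) | Family-wise error |
|---|---|
| 0 | 14.3% |
| 0.3 | 13.6% |
| 0.5 | 12.5% |
| 0.7 | 10.9% |
| 0.9 | 8.4% |

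**3. Power for each BMD site.** Same t-test formula, two-sided 5%. The first row is the quoted effect; the other two are assumed smaller effects at 24 weeks.

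| Standardised difference | 13 per arm | 17 per arm |
|---|---|---|
| 0.72 (Background, 18 months, men) | 42% | 53% |
| 0.5 (assumed) | 23% | 29% |
| 0.3 (assumed) | 11% | 14% |

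At 0.72, 80% power would need 32 per arm.

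**4. Power if all three must be significant (d = 1.53, 0.72, 0.72).**

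- It cannot exceed the power of the weakest test: 42% with 13 per arm, 53% with 17.
- If the outcomes are independent: 0.962 × 0.422 × 0.422 = 17% with 13 per arm; 0.991 × 0.530 × 0.530 = 28% with 17.

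**5. What an equal split of alpha would cost.** At 0.05/3 per test, SMI power is 90% with 13 per arm and 97% with 17. BMD power at 0.72 is 25% and 35%.

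**The case against.** The strongest reply is that this is a condensed article. A multiplicity rule is often placed in the full protocol or the analysis plan, neither of which is shown, and a general 5% level does not exclude a hierarchy there. That stands as far as the testing rule goes, and it is a reason not to rate the point higher. It does not remove the point. The article itself declares three primary outcomes, puts one level over all analyses and sizes on one outcome. An analysis plan can add a rule but cannot add power for BMD.

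Four stronger readings are tempting, and the document does not support them:

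- **That the protocol claims 95% power for BMD.** It does not. The 95% is attached to SMI, and on BMD power the protocol is silent.
- **That the family-wise error is a settled figure such as 13%.** Inflation requires the any-one rule, which is not stated, and a particular value requires correlations that are not given. What follows without a correlation is the 14.3% under independence.
- **That BMD power is near 8%.** This comes from scaling 0.72 linearly by 24/78 weeks to about 0.22. Nothing in the document supports linear growth; one can say only that a smaller effect at 24 weeks means lower power.
- **That a null BMD result will be taken as no effect.** This is speculation. The plan commits to 95% confidence intervals, and the Discussion already warns about the small sample.

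It is also fair to object that 42% is the low end. Intention-to-treat is specified and at least 17 per arm are enrolled, so 53% applies if everyone is analysed. The 0.72 is borrowed from men, over a longer period and with unequal protein intake between arms, and is not a design target here.

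**Conclusion.** The point holds and should be fixed. As written, the plan lets any one of three 5% tests support a claim, with a family-wise error of up to 14.3% (about 8% to 14% across the assumed correlations). If all three outcomes are required instead, error is controlled but power is at most 42% to 53%. Under either reading, each BMD outcome has 42% to 53% power at a standardised difference of 0.72.

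These figures assume the t-test branch of the analysis and 13 to 17 analysed per arm, and the BMD powers also assume that the earlier trial's effect carries over to women at 24 weeks. The SMI calculation itself is sound, and nothing here weakens an SMI conclusion tested alone at 5%.

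**What to change.** Before any between-group outcome data are seen, and in a dated amendment:

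1. Reconcile the hip site: the abstract has femoral neck, the outcome sections have total hip. The test sequence cannot be fixed until this is done.
2. Make change in SMI at 24 weeks the single primary outcome, tested at two-sided 5%.
3. Test lumbar spine BMD and then hip BMD as key secondary outcomes in fixed sequence, each at 5% and only if the preceding test is significant. This holds the family-wise error across the three at 5%.
4. Beside the sample size, state that the 95% power is for SMI only, and that BMD power is about 42% to 53% at an assumed standardised difference of 0.72 with 13 to 17 analysed per arm.

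**Cost.** Only wording changes. No participants are added, and SMI keeps the full 5% and its 96% power at 13 per arm. The price is that BMD cannot be claimed as confirmatory if SMI is not significant, and that bone moves to second place in a trial whose stated aim covers both tissues. If the sponsor prefers to keep three equal primary outcomes, an equal alpha split also controls error, at the powers in step 5 of the working. If outcome data have already been compared between arms, the reordering must be reported as made after the fact.
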